# Improving treatment for patients with childhood abuse related posttraumatic stress disorder (IMPACT study): protocol for a multicenter randomized trial comparing prolonged exposure with intensified prolonged exposure and phase-based treatment

**DOI:** 10.1186/s12888-018-1967-5

**Published:** 2018-12-12

**Keywords:** Posttraumatic stress disorder, CA-PTSD, Trauma focused treatment, Childhood trauma, Prolonged exposure, Phase-based treatment, Intensive treatment, STAIR

## Abstract

**Background:**

Childhood abuse related posttraumatic stress disorder (CA-PTSD) is associated with a high burden of disease and with treatment response rates that leave room for improvement. One of the treatments for PTSD, prolonged exposure (PE), is effective but has high drop-out rates and remission rates are relatively low. An intensified form of PE (iPE) was associated with good response and low drop-out rates in PTSD and has not yet been tested in a controlled trial in CA-PTSD. Phase-based treatment (PBT), in which PE is preceded by skills training may improve overall outcomes in this population. We will assess the effectiveness and cost-effectiveness of standard PE, iPE and PBT in patients with CA-PTSD.

**Methods/design:**

Multi-center randomized controlled trial. Treatment conditions are: prolonged exposure (PE; maximum of 16 sessions in 16 weeks); intensified PE (iPE; maximum of 12 sessions in four weeks and two booster sessions); phase-based treatment (PBT; maximum of eight sessions skills training followed by eight sessions PE in 16 weeks).

Primary outcome: Clinician-rated PTSD symptom severity. Secondary outcomes: loss of PTSD diagnosis, self-reported PTSD symptom severity, comorbid symptom severity and quality of life. Moreover, we will examine cost-effectiveness and moderators and mediators of treatment outcome. Target population: adults with CA-PTSD (*N* = 150). Assessments in weeks 0, 4, 8, 16, 26 and 52.

**Discussion:**

Given that no consensus yet exists about the treatment guidelines for patients with CA-PTSD, the present study may have important implications for the treatment of CA-PTSD.

**Trail registration:**

Registered at C.C.M.O. on Sept 7, 2016 (NL57984.058.16); retrospectively registered at June 21, 2017 at clinicaltrials.gov identifier: NCT03194113.

## Background

Childhood abuse is associated with severe negative long-term consequences. These include health problems, high health care utilization, a high risk of revictimization, low socio-economic well-being and criminal behavior in adulthood [1–6]. Childhood abuse is also related to many mental health problems such as depression, suicidality, dissociation, personality disorders, substance abuse and aggression [4, 5, 7–10]. In many cases, childhood abuse leads to Posttraumatic Stress Disorder (PTSD): 22 to 49% of those who report childhood abuse fulfill criteria for lifetime PTSD [11]. The treatment of PTSD in this population is relatively under investigated.

In international guidelines of PTSD, trauma-focused treatment (TFT) is recommended as first treatment option [12]. Substantial evidence exists for the effectiveness of TFT in patients with PTSD [13–15]. Treatment adherence and efficacy are relatively low, however. A meta-analysis indicated that 44% of the patients still fulfilled diagnostic criteria for PTSD at the end of treatment [14]. TFT may be less effective in CA-PTSD than in PTSD in general, because patients with CA-PTSD have more comorbid symptoms, such as interpersonal problems and emotion regulation difficulties [16]. These symptoms contribute significantly to functional impairment [17] but are not specifically addressed in TFT. This may lead to poorer outcomes and specifically less effective use of trauma focused interventions. The current study is designed to investigate the effectiveness of two variants of TFT that may lead to improved effectiveness and/or adherence compared to standard TFT.

Some authors [15, 18, 19] have argued that trauma focused treatment (TFT) is the preferred treatment for patients with CA-PTSD despite earlier mentioned comorbid symptoms in these patients. A recent meta-analysis indeed revealed more symptom improvement after TFT than non-TFT in patients with CA-PTSD [15]. A systematic review also concluded that there is no reason to exclude patients with CA-PTSD from TFT [20]. However, the comorbid symptoms may make it more difficult for those patients to attend weekly treatment sessions, and for therapists to keep the focus on trauma treatment. This has led some researchers to propose that treatment of patients with CA-PTSD may be improved by intensification of TFT. Promising results with an intensified form of TFT in PTSD [21–25] suggest that condensing treatment in a shorter period of time may lead to faster or better treatment results. Reduction of treatment length may not only lead to faster improvement, but also to improved treatment adherence, because there is less time between sessions for anticipatory anxiety to build up [24, 26]. Intensive TFT (up to 18 h of cognitive therapy (CT) delivered in one week) led to faster symptom reduction compared to standard TFT (up to 20 h of weekly CT sessions delivered in 3 months) and equivalent results over 14 weeks [23]. In a veteran population an intensified form of TFT led to faster symptom decline, while it was as effective as regular weekly TFT on the long term [22]. With regard to CA-PTSD, results of a controlled case series design with intensive TFT in adolescents (*N* = 10) also suggest that intensive treatment is safe and acceptable, with an 80% remission rate [24]. Furthermore, results of two open studies in patients with chronic PTSD following multiple traumas, including CA, [21, 25] show that intensive TFT was effective and patient retention high (less than 5% drop-out). Taken together, these studies suggest that intensive TFT (iTFT) may improve overall effectiveness of treatment of CA-PTSD.

Other authors [27–30] have argued that the symptoms and problems frequently observed in patients with CA-PTSD are characteristics of a distinct form of PTSD, referred to as ‘complex PTSD’. Complex PTSD is characterized by prominent emotion regulation difficulties, interpersonal problems and a negative self-concept [30]. The International Society for Traumatic Stress Studies (ISTSS) guidelines recommend ‘phase-based treatment’ as first treatment option for patients with complex PTSD [28]. In phase-based treatment (PBT) the first sessions are focused on addressing emotion regulation and interpersonal problems, which is followed by TFT [31]. This treatment is based on the notion that emotion regulation and interpersonal problems interfere with daily life functioning and that reduction or resolution of these problems can facilitate more effective use of TFT and can best be addressed before starting TFT [31]. PBT has indeed been associated with lower drop-out rates and more complete PTSD remission than supportive treatment followed by TFT [32].

Further research on the treatment of CA-PTSD is needed because of limitations of existing studies. Firstly, no studies have directly compared TFT with PBT or iTFT [15, 18, 33]. Secondly, patients with comorbidities such as dissociation, suicidality and personality disorders have often been excluded from RCTs, limiting the generalizability of the results to the population of CA-PTSD [15, 29, 34, 35]. Thirdly, in most studies participants were predominantly Caucasian and employed, while PTSD is more severe in patients who are unemployed or from minority ethnical backgrounds [15, 29, 36, 37]. Fourthly, many studies have methodological shortcomings such as a lack of blind assessments and no reported data on treatment integrity [15]. Allegiance effects – the unintentional bias due to investigators’ or therapists’ preferences [33, 38] – is a general problem in clinical research. This may be solved by involving researchers with different areas of expertise and allegiances [39].

### Current study

The aim of the current study is to examine the effectiveness of three different treatment strategies for patients with CA-PTSD. We will carry out a randomized controlled trial (RCT) comparing the (cost-)effectiveness and treatment adherence of a well-established form of TFT, prolonged exposure (PE), with two potential improvements of TFT: intensified PE (iPE) and phase-based treatment (PBT). For the iPE group, PE sessions are delivered in 4 weeks (3 sessions per week), PBT consists of Skills Training in Affective and Interpersonal Regulation (STAIR), followed by PE. We expect more PTSD symptom reduction and lower drop-out rates in iPE and PBT than in PE. We also expect that iPE and PBT will be more cost-effective, given that the treatment protocols include fewer (iPE) and shorter (PBT) sessions. We expect that iPE will lead to faster improvement than PE and PBT. Finally, we expect that PBT will be superior to both PE and iPE with respect to improvement in emotion regulation, interpersonal skills and self-esteem. The primary outcome is clinician-rated PTSD symptom severity. Secondary outcomes are loss of PTSD diagnosis, self-reported PTSD symptom severity, treatment adherence, comorbid symptoms severity and cost-effectiveness. Outcomes will be assessed at baseline, after 4, 8 and 16 weeks and at 6 and 12 months follow-up.

### Moderators and mediators

In line with previous work [40], we will investigate whether treatment effects are affected by baseline characteristics such as PTSD symptom severity, comorbid symptoms, emotional maltreatment and avoidance behavior, using between- and within-group moderation tests. We will calculate a ‘personalized advantage index’ (PAI) [41] and trees for treatment-subgroup interactions (QUalitative INteraction Trees; QUINT) to evaluate which pretreatment characteristics are most discriminating in predicting optimal treatment and differential response to treatments with a combination of predictor variables. This may lead to the development of optimal (personalized) treatment sequences [41–43].

As to mediators, moderately strong evidence exists that between-session habitation and change in post-traumatic cognitions mediate the effects of PE, while mixed evidence exists for emotional engagement, inhibition learning and within-session habituation [44]. Mediators of iPE are yet unknown. With regard to PBT, there is some evidence for the mediating effect of both emotion regulation improvement and therapeutic alliance on PBT outcome [31, 45]. More research on mediators is needed, as the number and quality of the studies are limited [44]. In the current study we will examine all above mentioned mediators.

## Methods

### Design

The IMPACT study is a multicenter RCT comparing prolonged exposure (PE) with intensified prolonged exposure (iPE) and phase-based treatment (PBT). Participants will be randomly assigned to the conditions. Figure 1 depicts the study flowchart. The research protocol has been approved by the Medical Ethical Committee of Leiden University Medical Center (NL57984.058.16), and is pre-registered at https://clinicaltrials.gov/ct2/show/NCT03194113.

**Fig. 1 Fig1:**
[figure not shown]
Flowchart of the IMPACT study

### Recruitment

Participants are recruited at the departments of Psychotrauma of PsyQ Den Haag and PsyQ Rotterdam. Referrals from other treatment centers will also be accepted. After initial screening, potential participants will receive written and oral information about the study. Patients who are interested in participating are invited for the baseline assessment including screening of in- and exclusion criteria and an informed consent procedure. Informed consent will be obtained prior to the assessment.

### Participants

Inclusion criteria of the study are: 1) age 18–65; 2) diagnosis of PTSD as established with the Clinician Administered PTSD Scale (CAPS-5, see instrument section), and at least moderate severity of PTSD-symptoms (CAPS ≥26), and with at least one specific memory for a traumatic event; 3) multiple traumata related to childhood sexual and/or physical abuse that occurred before 18 years of age, committed by a primary caretaker or an authority figure as index event; 4) sufficient fluency in Dutch to complete the treatment and research protocols.

Exclusion criteria are: 1) involvement in a compensation case or legal procedures concerning admission or stay in The Netherlands; 2) pregnancy; 3) severe non-suicidal self-injury (NSSI) which required hospitalization during the past three months; 4) severe suicidal behavior: a suicide attempt during the past three months or acute suicidal ideations with serious intent to die with a specific plan for suicide and preparatory acts; 5) severe disorder in the use of alcohol or drugs in last three months; 6) cognitive impairment (estimated IQ < 70); 7) changes in psychotropic medication in the two months prior to inclusion; and 8) engagement in any current psychological treatment.

### Sample size

Our sample size calculations are based on the intention to detect at least moderate effect size differences (d = .40) among conditions. To detect this effect size difference in PTSD severity with alpha = .05 (2-tailed) and a power of 0.8, 50 participants per condition are needed. We expect some drop-out which will result in a lower power due to missing values. However, we calculated the sample size based on the conservative assumption that the correlation between the baseline and all further post measurements is 0 and the correlation between post measurements is 1, since we do not have a good estimation for the correlation between the outcome measurements yet. Thus, the actual power is expected to be considerably higher than 0.8 due to the multiple measurement design correcting for power loss due to drop-out [46, 47].

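### With 50 patients per arm and the plan's own assumptions, power at d = 0.40 is about 51%, not 80%; 80% is reached only at d of about 0.57

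*Protocol article*

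**What the plan says.** The Sample size section says the calculation is "based on the intention to detect at least moderate effect size differences (d = .40) among conditions", and that "with alpha = .05 (2-tailed) and a power of 0.8, 50 participants per condition are needed". The abstract gives the matching total of 150 patients in three arms.

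The section then describes the basis as conservative, because it assumes that "the correlation between the baseline and all further post measurements is 0 and the correlation between post measurements is 1". The reason given is that no good estimate of the correlations was available. Drop-out is expected to lower power, but no rate is given and no patients are added for it. The section concludes that "the actual power is expected to be considerably higher than 0.8 due to the multiple measurement design correcting for power loss due to drop-out".

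The hypotheses under Current study make the main contrasts pairwise: iPE and PBT are each expected to reduce PTSD symptoms more than PE.

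**The concern.** The two correlations are the worst case for a repeated-measures design. If baseline says nothing about later scores, adjusting for it removes no variance. If all later scores are perfectly correlated, five visits carry the information of one. What remains is a two-sample comparison of single scores, and for that comparison 50 per arm is about half the number usually needed at d = 0.40.

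This is the only power justification in the article, and it concerns the primary outcome. A reader who trusts it would believe that a true difference of 0.40 SD is very likely to be detected. Under the stated assumptions it would be missed about half the time. A non-significant result could then be taken as a sign that the three treatments perform alike, when the trial could not tell.

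**Working it through.** **Inputs, all from the Sample size section:** d = 0.40 (so SD = 1), two-sided alpha 0.05, power 0.80, n = 50 per condition, baseline-post correlation 0, post-post correlation 1.

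**Step 1: reduce the design.** For the mean of m post measurements adjusted for baseline, the variance relative to a single unadjusted score is

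v = (1 + (m − 1)·r_post)/m − r_base²

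With r_post = 1 and r_base = 0, v = 1 for any m. The ordinary two-sample formula applies.

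**Step 2: try to reproduce 50 per arm.**

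n per arm = 2 × (1.96 + 0.8416)² / 0.40² = 2 × 49.06 = 98.1, so 99. The t-test calculation gives 99.1, so 100.

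The stated 50 is not reproduced. It is close to 49.06, which is the same expression without the factor 2 for two independent groups. That is consistent with a one-sample or paired formula having been used, but the article gives no formula, so the cause is an inference and the finding does not depend on it.

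**Step 3: power with 50 per arm.** The standard error is √(2/50) = 0.20, and 0.40/0.20 = 2.00. The normal approximation gives Φ(2.00 − 1.96) ≈ 0.516; the noncentral t gives 0.508.

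**Step 4: effect detectable with 80% power.** (1.96 + 0.8416) × 0.20 = 0.560; the t-test gives 0.566. The 95% confidence interval has a half-width of 1.96 × 0.20 = 0.39 SD, about as wide as the target effect.

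**Step 5: other readings at d = 0.40 and 50 per arm.**

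| Reading | Power |
|---|---|
| One-sided test | 0.63 |
| iPE and PBT pooled against PE (100 v 50) | 0.63 |
| Three-group omnibus test, means 0/0.4/0.4 | 0.52 |
| Three-group omnibus test, means 0/0.2/0.4 | 0.41 |
| Change score with correlation 0 | 0.29 |
| Bonferroni, alpha 0.025 | 0.40 |

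None reaches 0.80. A single post score adjusted for a baseline correlated at 0.70 would need 51 per arm, but that contradicts the stated correlation of 0.

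**Step 6: drop-out.** The article gives no rate. Assuming 10%, 20% or 30% loss with nothing recovered from those patients, t-test power falls to 0.47, 0.42 or 0.38. With 20% loss the detectable effect is d = 0.63.

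**Step 7: what repeated measures could give.** The correlations here are assumptions. The estimand is the average over five post-baseline visits, adjusted for baseline, with t-test power at d = 0.40.

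| r_base | r_post | v | No loss | 20% loss |
|---|---|---|---|---|
| 0.5 | 0.5 | 0.35 | 0.92 | 0.85 |
| 0.6 | 0.7 | 0.40 | 0.88 | 0.80 |
| 0.5 | 0.6 | 0.43 | 0.86 | 0.77 |
| 0.5 | 0.7 | 0.51 | 0.79 | 0.70 |
| 0.3 | 0.6 | 0.59 | 0.73 | 0.63 |
| 0.5 | 0.8 | 0.59 | 0.73 | 0.63 |

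For one time point with r_base = 0.5, v = 0.75 and power is 0.63.

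**The case against.** The best defence is that 0.51 describes a worst case and not the analysis that will be run. The Analyses section plans a multilevel repeated-measures model, and Table 1 schedules the CAPS-5 at baseline and five later visits. With moderate correlations, the average-over-visits contrast can exceed 0.80, as Step 7 shows. The direction of the article's claim is therefore right: actual power should be higher than under correlations of 0 and 1. The 20% loss is also an assumption of this check, and the loss figures are pessimistic in treating lost patients as contributing nothing, since the plan includes all randomised patients with multiple imputation.

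These points limit the statement of impact. Missing a true difference about half the time applies under the stated correlations and not necessarily to the final analysis. They do not rescue the figure. The section says the 0.8 was calculated before any gain from repeated measures, so the same gain cannot also be what produces it. It also says no good estimate of the correlations exists, so no favourable value is supported. Finally, the gains in Step 7 are for an average over all five visits; a contrast at one visit gains much less.

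**Conclusion.** The stated sample size and power contradict the inputs printed beside them. With d = 0.40, two-sided 5%, 50 per arm and correlations of 0 and 1, power is 0.51. Eighty per cent power needs 99 to 100 per arm, or is reached at d of about 0.57 with 50. These results use only the article's own inputs and hold before drop-out.

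The claim that power will be considerably above 0.8 has no support as written. Part or all of any repeated-measures gain is needed just to climb from 0.51 to 0.80. Whether actual power ends above or below 0.80 depends on correlations, drop-out and the choice of contrast, none of which the section fixes at a realistic value. The power statement needs correcting.

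**What to change.** Keep N = 150 and correct the statement. Suggested wording: With 50 patients per condition and two-sided alpha .05, power is about 0.51 for d = 0.40; 80% power is reached at d = 0.57 under the stated correlations, before drop-out.

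Replace the sentence about power being considerably higher than 0.8 with a power range over named baseline-post and post-post correlations and drop-out rates, saying whether the contrast is at one visit or averaged over visits. If the investigators believe particular correlations support 50 per arm, they should name and justify them in place of 0 and 1.

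It would also help, though it is separate from the arithmetic, to commit to reporting confidence intervals for each pairwise difference and to not reading a non-significant result as similarity.

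The cost is a less favourable printed figure. No extra patients, visits or analyses are needed.

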### Procedure

Before randomization, patients complete a baseline assessment of the study. In the preparatory session, patients receive detailed information about the treatment and research procedures and about practical considerations, such as availability. Randomization is carried out by an independent researcher from Leiden University who uses a computerized randomization sequence of permutated blocks of six patients, stratified by gender. Patients are regarded as treatment drop-out if they stop therapy prematurely and as measurement drop-out if they refuse or do not show up for follow-up measurements. Early responders are defined by a score below 16 on the PTSD checklist for DSM-5 (PCL-5) for three consecutive weeks with agreement between patient, therapist and supervisor about finishing the therapy early [48, 49]. Measurements will take place at baseline, during the therapy (after 4 weeks, 8 weeks and 16 weeks) and follow-up measurements after 6 and 12 months. All measurements are performed by trained and supervised interviewers, who are blind to treatment condition. Patients and their therapists also fill out self-report questionnaires before therapy sessions and fill out questionnaires about harm expectancies and distress during the exposure therapy.

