### Methodological considerations

We expect to include a cultural and socioeconomic diverse sample, since the participating centers are located in large cities. We protect the generalizability of the findings by using few exclusion criteria. The relatively long follow-up measurements of 6 and 12 months will provide insights in the long-term effects of the therapies. Every type of treatment is supervised by expert supervisors of that specific method. Additionally, all therapists are trained and supervised in both PE and PBT. This prevents biases to the internal reliability of the study and is essential for a meaningful interpretation of the results [39].

Limitations of this study are that not all eligible patients will agree to participate in the study which could result in selection bias. Especially the iPE condition could lead to selection bias since it is more demanding in terms of time investment in the first weeks of the treatment. All reasons of patients to decline participation in the study will be carefully monitored to ensure the generalizability of the results and for implementation purposes. Another limitation is that patients have one therapist in PE and PBT, but two alternating therapists in the iPE condition. This may influence the therapeutic alliance and consequently the results of the treatment. We will assess whether therapeutic alliance indeed differs between condition and, if so, whether this has any influence on treatment results.

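### A single disclosed block size of six, stratified by gender only, makes up to one allocation in five certain to anyone able to follow every assignment within a gender stratum at both sites

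*Protocol article*

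**What the plan says.** The Procedure section states "Randomization is carried out by an independent researcher from Leiden University", using "a computerized randomization sequence of permutated blocks of six patients, stratified by gender". No other block size and no other stratification factor is named.

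The Sample size section says "50 participants per condition are needed", which with three conditions implies 1:1:1 allocation. The Recruitment section says "Participants are recruited at the departments of Psychotrauma of PsyQ Den Haag and PsyQ Rotterdam". Since site is not a stratum, both departments as written draw on the same two gender sequences.

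On blinding, the Procedure section says "All measurements are performed by trained and supervised interviewers, who are blind to treatment condition". Nobody else is described as blind. The treatment sections describe schedules that cannot be hidden from those who deliver them: weekly exposure in PE, three sessions a week shared by two therapists in iPE, and skills training first in PBT. The Therapists and training section adds that every location runs all three treatments under common weekly supervision.

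**The concern.** Having an independent researcher hold the list conceals the list itself. It does not stop someone who knows the block size from working out the remaining places from the allocations already made. With one fixed size, stated in a public article, the end of each block gives itself away to anyone keeping a tally.

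The arms differ in ways that could matter to staff. iPE is the most time-intensive at the start, and the preparatory session, described just before randomisation, informs patients "about practical considerations, such as availability". The Background also names allegiance effects as a general problem in clinical research. If a person who influences the timing or encouragement of enrolment could foresee that the next place is, or cannot be, iPE, patient selection could come to differ between arms. Randomisation is meant to exclude exactly that.

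**Working it through.** The article gives no figure for predictability, so there is none to reproduce.

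**Inputs**
- Block size 6, single (Procedure).
- Three arms of 50 (Sample size), hence two places per arm in each block. The ratio is inferred from the equal targets.
- 150 patients in total (Abstract, Methods/design).
- Two recruiting departments, with site not a stratum (Recruitment, Procedure).

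**Step 1: observer with full information.** This observer knows every earlier allocation in the stratum and the block boundaries. A block has 6!/(2!·2!·2!) = 90 equally likely orderings. By position in the block, the probabilities are:

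| Position | Allocation certain | At least one arm ruled out | Best guess correct |
|---|---|---|---|
| 1 | 0 | 0 | 1/3 |
| 2 | 0 | 0 | 2/5 |
| 3 | 0 | 1/5 | 1/2 |
| 4 | 0 | 3/5 | 8/15 |
| 5 | 1/5 | 1 | 3/5 |
| 6 | 1 | 1 | 1 |
| Sum | 6/5 | 14/5 | 101/30 |
| Sum ÷ 6 | 20.0% | 46.7% | 56.1% |

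Over 150 patients this is 28.8 to 30 certain allocations, depending on the gender split. If both strata fill complete blocks, 25 × 1.2 = 30. If both end on an incomplete block (for example 75 and 75), 24 × 1.2 = 28.8.

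For iPE alone, the observer knows whether the next place is or is not iPE when both iPE places are used or when only iPE places remain. Summed over positions, the first has probability (1 + 3 + 6 + 10)/15 = 20/15 and the second (1 + 5)/15 = 6/15. The total is 26/15, and dividing by 6 gives 28.9%.

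**Step 2: observer with partial information.** Suppose the observer knows the position in the block but has seen each earlier arm only with probability p. Certainty requires having seen all four places of the other two arms, which has probability p⁴. The share of certain allocations is therefore p⁴ × (1/5 + 1)/6 = 0.2 × p⁴.

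| Share of earlier arms seen | Allocations certain |
|---|---|
| 100% | 20.0% |
| 90% | 13.1% |
| 70% | 4.8% |
| 50% | 1.25% |

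The 50% row corresponds to one of two equally recruiting sites, and the equal split is an assumption. An observer at one site who does not know how many patients the other site has enrolled does not know the position in the block and can never be certain.

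**Step 3: varied block sizes.** This was simulated over 300 trials of 150 patients. The observer sees the whole sequence and knows the set of sizes, but not the current one.

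| Sizes | Allocations certain | Best guess correct |
|---|---|---|
| 6 only | 20% | 56% |
| 6, 9 | 5.0% | 54% |
| 3, 6, 9 | 3.8% | 55% |
| 6, 9, 12 | 2.4% | 53% |

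A separate simulation of 4,000 blocks with sizes 6, 9 and 12 also gave 2.4% certain, with at least one arm ruled out for 7.2% of allocations and a best guess of 53%.

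**The case against.** The strongest reply is that a reader might infer from the 20% that staff at the sites know one allocation in five. The article describes no such observer. One unstratified-by-site sequence serves two departments, an independent researcher holds it, and nothing says that therapists or supervisors track allocation order by gender. Shared supervision makes pooled knowledge possible, not documented. This objection stands, and the 20% must be read as an upper bound.

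Second, a reader might infer biased enrolment. The Recruitment section places eligibility screening and consent at the baseline assessment, and the Procedure section has all measurements done by interviewers stated to be blind. The article does not say who conducts the initial screening or the preparatory session, nor that therapists decide on or time entry. The remark "Especially the iPE condition could lead to selection bias since it is more demanding in terms of time investment" does not fill that gap: it concerns eligible patients declining the whole trial, which limits generalisability and does not in itself distort the comparison between arms.

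Third, it is tempting to say that the block size was published while patients were being enrolled. The present and future tense of the December 2018 article, and the abstract's note of retrospective registration in June 2017, make this plausible. No recruitment start or end date is given, so it remains an inference.

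Fourth, fixed blocks held by an independent party are a usable design, and varying them barely lowers the best-guess rate. Both points are fair. What survives is that the article commits to one size and discloses it, and that fully certain allocations, the most exploitable kind, can be nearly removed at little cost.

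**Conclusion.** The concern holds as a modest, avoidable weakness in allocation concealment. The 20% figure is exact for three arms at 1:1:1 in blocks of six, but only for someone who sees every earlier assignment in a gender stratum across both sites and knows the block boundaries. It falls to 4.8% if 70% of earlier arms are seen and to about 1% if half are seen, even when the position in the block is known.

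Two links rest on inference. That therapists know the arms follows from the treatments and is safe to assume. That anyone with such knowledge influences enrolment is not stated. The documents therefore support no claim that selection occurred or that the arm comparison is biased. Nothing in the article is miscalculated or contradictory on this point; it is a design choice that could be better.

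**What to change.** For any patients still to be randomised, the independent researcher should generate the remaining gender-stratified list with randomly varying block sizes in multiples of three. The sizes should be kept from the sites and out of public documents until recruitment ends, and the date of the change recorded.

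The cost is a new computer list and one line in the protocol. The drawback is slightly looser balance. A block of 12 holds four places per arm, so an incomplete last block can leave two arms up to 4 apart within a gender stratum, against 2 with blocks of six.

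If recruitment has closed, the list cannot be changed. The trial report should then say who could see past allocations, at which site, and whether those people had any part in screening or enrolment.
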